#### Protocol

The overall protocol timeline is detailed in Figure 1. Briefly, between 24 h and 7 days post-ICU admission, high-density EEG will be recorded from continuously-sedated brain-injured patients before, during, and after a brief interruption of their pharmacological sedative. Brief interruptions of sedation are routinely performed in standard clinical practice for most brain-injured patients in the ICU to assess for clinical stability and behavioral reactivity. Among patients who subsequently regain consciousness during or following their ICU stay, we will prospectively track neurocognitive and functional outcomes up to 12 months post-injury, using an abridged CBS battery and follow-phone interviews.

**FIGURE 1 F1:**
[figure not shown]
General timeline of overall study measures. Continuously-sedated brain-injured patients will be recruited from the ICU and have their brain activity recorded before, during and after a brief interruption of continuous sedation, using high-density EEG between 24 h and 7 days post-injury. Once patients recover consciousness, they will be screened daily for delirium. Once they have been confirmed delirium-free, they will begin taking neurocognitive tests using the Cambridge Brain Sciences (CBS) battery on a daily basis, or as often as possible, until there are discharged from the hospital. Up to 3 months following their first CBS test, patients will continue to take the CBS battery on a weekly basis. After the initial 3 months of intensive neurocognitive testing, patients will be asked to complete the CBS battery on a monthly basis, up to 12 months post-injury. A phone assessment will also take place 3 months following the recovery of consciousness (i.e., start of CBS test), and at 6 and 12 months post-injury, to assess functional outcome using the Glasgow Outcome Scale-Extended and the Disability Rating Scale. ICDSC, Intensive Care Delirium Screening Checklist; ICU, Intensive Care Unit.

#### Demographic and Clinical Characteristics

For screening and to characterize the association between our EEG and neurocognitive markers and demographic and acute critical illness characteristics, we will record: age; sex; occupation; level of education; ethnicity; languages spoken; pre-morbid medical history (including neurocognitive and psychiatric disorders); and pre-morbid substance use; injury type (e.g., traumatic, anoxic); mechanism of injury; Glasgow Coma Scale score; severity illness score (SOFA and MODS); CT scan findings (e.g., Marshall and Rotterdam scores); presence and duration of intracranial pressure (if monitored); visual fixation; sedation/analgesia drug levels; delirium duration; post-traumatic amnesia duration; ICU stay duration, and hospital stay duration. For all sedatives and analgesics received in the 24 h prior to the EEG recording, we will also record the doses, types and administration routes and times.

#### High-Density EEG

This protocol will be conducted using a 128-channel EEG recording system from Electrical Geodesics, Inc. (Eugene, OR, United States) with sponge-based electrode nets, which provides the ability to set up all electrodes in approximately 10 min. Consented participants at each site will be outfitted with this EEG system at their bedside 30 min prior to a planned clinical cessation of continuous sedation. The bedside EEG recording will take place in three phases: (1) baseline continuous sedation (i.e., when patients are continuously sedated); (2) interruption of sedation (i.e., after continuous sedation has been interrupted for clinical assessment); and (3) return of sedation (i.e., 20 min after continuous sedation has been restarted) (see Figure 2).

**FIGURE 2 F2:**
[figure not shown]
Schematic timeline of EEG recordings before, during, and after a brief interruption of continuous sedation. In the ICU, between 24 h and 7 days post-injury, continuously-sedated brain-injured patients will have their brain activity recorded using high-density EEG during 10 min at resting state, under continuous sedation (EEG Recording 1). The clinical team will then interrupt sedation to carry out their neurobehavioral assessment, as standard of care. Following this assessment, sedation will continue to be withheld for 15 additional minutes, during which EEG will be recorded for 5 min at resting state, and 10 min during which an auditory narrative will be played through headphones, in its scrambled (5 min) and intact form (5 min) (EEG Recording 2). Twenty minutes after continuous sedation is reinstated, a final 10-min resting state EEG recording will take place (EEG Recording 3).

##### EEG recording 1 – baseline continuous sedation

Prior to the scheduled cessation of sedation, participants will have their brain activity recorded for 10 min at resting state.

##### EEG recording 2 – interruption of sedation

Sedation will be stopped, and clinicians will conduct their clinical neurobehavioral assessment, as per standard of care. The EEG net will remain on the participant’s head during this time. Once sedatives have been withheld and the clinical neurobehavioral assessment has been completed, participants will remain without sedation for a maximum of 15 additional minutes – or as long as the patient is tolerating it and the medical team deems it safe [i.e., vitals remain stable and intracranial pressure remains normal (<20 mmHG)] – during which brain activity will be recorded with EEG for the study. Of these 15 min of EEG recording, 5 min will be recorded at resting state and 10 min will be recorded while the patient is listening to an auditory narrative intended to evoke evidence of higher cognitive functioning, including covert awareness (Naci et al., 2017). We will use the auditory narrative paradigm to look for evidence of covert awareness during the interruption of continuous sedation. Patients will have headphones placed over their ears for 10 min while EEG is recorded during the interruption of sedation. We will play a 5-min scrambled audio segment of the motion picture *Taken*, and subsequently play the unscrambled audio of the same 5-min segment.

As patient safety will be prioritized, sedatives will be reinstated as standard of care after the 15 min of EEG recording, or as soon as the clinical team decides to do so, whether or not the EEG recording is complete.

##### EEG recording 3 – return of continuous sedation

Twenty minutes following the return of continuous sedation, participants will have their brain activity recorded for 10 min at resting state, at which point the EEG recording will be discontinued.

### EEG Data Analysis

#### EEG Pre-processing

Data will be pre-processed using EEGlab (Delorme and Makeig, 2004). Data will be bandpass filtered between 0.1 and 50 Hz and all artifacts will be removed. All non-brain electrodes will be removed from subsequent analyses. Data will be segmented into the three phases of the EEG recording: (1) baseline continuous sedation; (2) interruption of sedation; and (3) return of continuous sedation.

#### Spectrogram and Topographic Maps

Spectrograms ranging from 0.1 to 50 Hz, and topographic maps of each frequency band [delta (1–4 Hz), theta (4–8 Hz), alpha (8–13 Hz), beta (13–30 Hz)], and phase-amplitude coupling measures will be used to characterize the EEG in each phase, and will be calculated semi-automatically through the designated pipeline EEGapp (Biosignal Interaction and Personhood Technology Lab, McGill University).

#### Functional Connectivity

Functional connectivity between all potential electrode pairs will be assessed with the weighted phase lag index (wPLI) (Vinck et al., 2011), which avoids confounds of volume conduction (Stam et al., 2007). First, cleaned EEG data will be segmented into delta (1–4 Hz), theta (4–8 Hz), alpha (8–14 Hz), and beta (14–30 Hz) frequency bands using band-pass filtering methods. wPLI will be calculated using the following formula:

$$w\,P\,L\,I_{i\,j}=\frac{\left|E\,\left\{𝒥\,\left(C_{i\,j}\right)\right\}\right|}{E\,\left\{\left|𝒥\,\left(C_{i\,j}\right)\right|\right\}}=\frac{\left|E\,\left\{\left|𝒥\,\left(C_{i\,j}\right)\right|\,s\,g\,n\,\left(𝒥\,\left(C_{i\,j}\right)\right)\right\}\right|}{E\,\left\{\left|𝒥\,\left(C_{i\,j}\right)\right|\right\}}$$

where *𝒥*(*C*_*ij*_) is the imaginary part of cross-spectrum *C*_*ij*_ between signals *i* and *j* (Vinck et al., 2011). The cross-spectrum *C*_*ij*_ is defined as Z*_*i*_*Z*_*j*_*^∗^, where Z*_*i*_* is the complex value Fourier spectra of the signal i for each frequency, and Z*_*j*_*^∗^ is the complex conjugate of Z*_*j*_*. *C*_*ij*_ can be written as *Reiθ*, where R is magnitude and *θ* is the relative phase between signal *i* and *j* (Vinck et al., 2011). A wPLI value of 1 indicates complete phase locking between the two signals (i.e., that the instantaneous phase of one signal is leading the other). Conversely, a wPLI value of 0 indicates no consistent phase-lead or -lag relationship.

In order to characterize the direction of functional connectivity (i.e., the direction of phase-lead/lag relationship between channels *i* and *j* in the wPLI matrix), we will calculate the directed phase lag index (dPLI) (Stam and van Straaten, 2012). The instantaneous phase of each EEG channel will be extracted using a Hilbert transform, and the phase difference Δ*φ*_*t*_ between all the channels will be calculated where Δφ_*t*_ = φ_*i*,*t*_−Δφ_*j*,*t*_, t = 1,2,…,N, where N is the number of samples in one epoch, and *i* and *j* include all channels. dPLI will then be calculated using the following formula:

$$d\,P\,L\,I_{i\,j}=<H\,\left(\Delta \,\varphi_{t}\right)>$$

where H(x) represents the Heaviside step function, where H(x) = 1 if x > 0, H(x) = 0.5 if x = 0 and H(x) = 0 otherwise. A dPLI value ranging from 0.5 to 1 will indicate that signal *i* leads signals *j*, whereas a dPLI value between 0 and 0.5 will indicate the reverse. If there is no phase-lead/phase-lag relationship between signals, dPLI = 0.5.

For both the wPLI and dPLI matrices, we will control for noise-induced phase relationships using surrogate datasets in which the phase relationship between two channels will be randomized, but their spectral properties maintained. Data segments used to generate surrogate wPLI/dPLI matrices will be 10 s in length, and will be permuted 20 times to generate a distribution of values representing the spurious connectivity. The wPLI and dPLI values of the original, non-shuffled EEG data will then be compared to this distribution of surrogate data using a Wilcoxon signed rank test and will be set to 0 (wPLI) or 0.5 (dPLI) if they do not achieve statistical significance.

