#### Graph Theoretical Brain Network Properties

The functional brain network of each frequency band (i.e., delta, theta, alpha, beta) will be constructed using the wPLI of all pairwise combinations of electrode channels. We will then construct a binary adjacency matrix A_*ij*_ using a custom threshold for each participant: if the wPLI*_*ij*_* value of nodes *i* and *j* are above the custom threshold of all wPLI values, A*_*ij*_* = 1; otherwise, A*_*ij*_* = 0. The custom threshold will be determined by identifying the lowest threshold enabling a minimally-spanning graph during the interruption of sedation, which will be considered the more naturalistic brain network of the three recordings. This will enable a more accurate construction of each patient’s brain network, based on how their brain injury affects connectivity characteristics. From the binary adjacency matrix, we will calculate basic graph theoretical network properties, including global efficiency (Latora and Marchiori, 2001), clustering coefficient (Watts and Strogatz, 1998), modularity (Newman, 2006), and binary small-worldness (Humphries and Gurney, 2008).

Hub nodes are highly-connected nodes, considered to play a vital role in the structure of a network and the flow and integration of information within the network (van den Heuvel and Sporns, 2013). In healthy individuals, their structure and topographical location become altered under anesthesia (Lee H. et al., 2013) Using the network of each frequency band, network hubs will be calculated using node degree (i.e., the number of edges connected to a node) and betweenness-centrality (i.e., the number of shortest paths passing through a node).

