to calculate the cross-covariance across all electrodes x and time *t* between participant *k* and *l*. Therefore, eigenvectors w*_*i*_* of the cross-covariance matrix R*_*w*_*^–1^R*_*b*_*, with the largest eigenvalues λ*_*i*_* computed as (R*_*w*_*^–1^R*_*b*_*)w*_*i*_* = λ*_*i*_*w*_*i*_* are the components that maximize Pearson’s rho between subjects (Dmochowski et al., 2012; Cohen and Parra, 2016; Ki et al., 2016). The CorrCA produces *N-1* components that are rank-ordered by the magnitude of their correlation across subjects, where *N* is the number of input sources (electrodes). The spatial weights of the top-ranked group-level component can then be back-projected onto the EEG data from individual subjects—effectively creating a spatial filter of the data—to generate a component time course for each participant. We will then correlate the individual component time courses across the group and compute the average correlation coefficient on a per-subject basis to compute individual inter-subject correlations which reflects the similarity of each participant’s neural activity relative to the group (Cohen and Parra, 2016; Ki et al., 2016; Iotzov et al., 2017).

The reliability of the CorrCA component and the statistical significance of the inter-subject correlations can be established using a leave-one-out variant of the CorrCA and permutation statistics. Specifically, the CorrCA is iteratively calculated on all possible *N-1* subsets of the group. This produces unique components and time courses for each subset which can be used to calculate the average inter-subject correlations for each participant *across* subsets. Statistical significance of the per-subject means inter-subject correlations can then be determined by comparing their magnitude to the top 5% (*p* < 0.05, FDR corrected) of a null distribution of phase-shifted correlation coefficients generated using a 1000 iteration resampling procedure (Theiler et al., 1992). This analysis technique will be applied to the EEG data from individual patients to compare their neural activity during the intact and scrambled versions of *Taken*.

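### As worded, the surrogate filter for wPLI and dPLI tests whether the surrogates' centre differs from the observed value, so it would keep about a third to two thirds of purely spurious connections

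*Protocol article*

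**What the plan says.** The purpose is stated in the Functional Connectivity section: "we will control for noise-induced phase relationships using surrogate datasets". The section then fixes the procedure:

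- Segments: "Data segments used to generate surrogate wPLI/dPLI matrices will be 10 s in length".
- Reference distribution: these "will be permuted 20 times to generate a distribution of values representing the spurious connectivity".
- Comparison: the original wPLI and dPLI values "will then be compared to this distribution of surrogate data using a Wilcoxon signed rank test".
- Consequence: values "will be set to 0 (wPLI) or 0.5 (dPLI) if they do not achieve statistical significance".

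The section gives no significance level, no sidedness and no pairing of observed and surrogate values across epochs.

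Two later sections use the result. In Graph Theoretical Brain Network Properties, the network is "constructed using the wPLI of all pairwise combinations of electrode channels" and is then binarised at a patient-specific threshold. In EEG Features Across Changes in Sedation Status, changes in wPLI, dPLI, graph properties and hubs between the three recording phases become predictors of outcome.

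The Auditory Narrative section handles a similar problem differently. There, significance "can then be determined by comparing their magnitude to the top 5" per cent of a null distribution built from 1000 resamples.

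**The concern.** A surrogate test should ask whether the observed value would be unusual if only noise were present, that is, whether it lies in the tail of its surrogates. A one-sample signed-rank test of the surrogates against the observed value asks something else: whether their centre is shifted away from that value. If a connection is pure noise, the observed value is one more draw from the surrogate distribution. A single draw seldom sits at the centre, so the test rejects often by construction. The more surrogates there are, the more precisely the centre is located and the more often the test rejects.

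In a two-sided form the test also keeps wPLI values that are significantly below their surrogates, which is no evidence of connectivity.

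The filtered matrices feed the reconfiguration predictors, and the main hypothesis under Anticipated Results concerns feedback-dominant fronto-parietal connectivity and posterior alpha hubs. Noise links that come and go between phases would blur that signal.

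**Working it through.** The plan states no error rate for this step, so there is no figure to reproduce.

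**Inputs from the article.** There are 20 surrogates per comparison, 10-s segments and a signed-rank test; non-significant values are set to 0 or 0.5.

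**Assumptions.** The level is 0.05, borrowed from the 5% used in the Auditory Narrative section. Both sidednesses are computed. One observed value is compared with its own 20 surrogates.

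**Critical values.** The exact null distribution of the signed-rank statistic for n = 20 gives rejection at W ≤ 60 one-sided (size 0.0487) and W ≤ 52 two-sided (size 0.0484).

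**Approximation, normal case.** In surrogate-SD units, the test has the precision of about 20 × 3/π = 19.1 observations.

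- It rejects when the observed value is more than 1.645/√19.1 = 0.376 SD (one-sided) or 1.96/√19.1 = 0.448 SD (two-sided) from the estimated centre.
- Under pure noise, that distance has SD √(1 + 1/19.1) = 1.026.
- One-sided: P(Z > 0.376/1.026) = P(Z > 0.367) ≈ 0.36.
- Two-sided: P(|Z| > 0.448/1.026) = P(|Z| > 0.437) ≈ 0.66.

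**Simulation with exact critical values.** The observed value and its 20 surrogates are exchangeable; 200,000 replicates per shape. The last column is two-sided minus two-sided-and-above.

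| Null shape | One-sided | Two-sided | Two-sided, kept although below surrogates |
|---|---|---|---|
| Normal | 0.349 | 0.643 | 0.643 − 0.320 = 0.323 |
| Half-normal | 0.321 | 0.665 | 0.665 − 0.295 = 0.370 |
| Rayleigh | 0.336 | 0.654 | 0.654 − 0.309 = 0.345 |
| Beta(2,8) | 0.326 | 0.655 | 0.655 − 0.299 = 0.356 |
| Exponential | 0.298 | 0.653 | 0.653 − 0.272 = 0.381 |
| Lognormal | 0.276 | 0.634 | 0.634 − 0.249 = 0.385 |
| Uniform | 0.379 | 0.706 | 0.706 − 0.354 = 0.352 |

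Separate runs with normal, half-normal and gamma shapes gave about 31–35% one-sided and 64–66% two-sided. The full span over the seven shapes above is 28–38% and 63–71%.

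**Simulated noise channels.** These were 3,000 independent pairs, 10 s, 8–14 Hz, with 250 Hz sampling assumed and actual wPLI and dPLI computed. wPLI was kept in 33–34% one-sided and 68–69% two-sided; dPLI in 35% and 65–66%.

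**More surrogates, normal case.**

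| Surrogates | One-sided | Two-sided |
|---|---|---|
| 100 | 43% | 84% |
| 1000 | 48% | 95% |

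**Rank rule on the same data.** Keeping a value only if it exceeds all 20 surrogates has a false-keep rate of 1/21 = 4.8% (4.1–4.8% in the noise channels). A two-sided rank rule with 20 surrogates cannot go below 2/21 = 9.5%. Two-sided 5% needs at least 39 surrogates, since 2/40 = 5%.

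**Alternative reading, paired across epochs.** With 30 or 60 segments (5 or 10 min of 10-s epochs), the false-keep rate was 3–7% when each observed value was paired with one surrogate, and 2–9% when paired with the surrogate mean.

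**The case against.** The strongest objection is that the article never says a single observed value is tested. It speaks of values in the plural and of 10-s segments, the signed-rank test is commonly used as a paired test, and a 10-min recording holds about 60 such segments. Paired across segments, the error rate is close to nominal. A condensed article might have dropped that detail. This stands as a reason to make the finding conditional. It does not remove it: the text describes comparison with a distribution formed by 20 permutations, and no pairing.

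Several stronger readings are tempting but not supported:

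- **That the plan misses its own 5% target.** The section states no level; 0.05 is an assumption.
- **That most noise passes.** This holds only for the two-sided form. One-sided, it is about a third.
- **That thousands of spurious links per band follow.** With 128 channels there are 128 × 127/2 = 8,128 pairs. EEG Pre-processing removes non-brain electrodes, and a count of spurious links would require every pair to be noise.
- **That all network predictors are equally contaminated.** Graph properties and hubs pass the later patient-specific threshold, which may drop some weak spurious edges. It is not a noise test, however, and it is not applied to dPLI.
- **That prognostic accuracy would be falsely inflated.** This is a preprocessing step, and the classifiers are to be evaluated by leave-one-subject-out cross-validation when applicable. Retained noise would mainly weaken the signal.
- **That lack of a correction over electrode pairs is an error.** An article may leave this to the full plan, and correcting an edge-screening step is a matter of preference.

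**Conclusion.** The concern holds in conditional form. As worded, the test addresses the surrogates' centre and does not do the job the section gives it. If one observed value is tested against its 20 surrogates at 0.05, about 31–35% (one-sided) or 64–66% (two-sided) of purely spurious connections survive. Raising the number of surrogates while keeping this test makes matters worse.

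The result rests on three inferences: the single-value comparison, the 0.05 level, and exchangeability of observed and surrogate values under noise. Both sidednesses fail. Only pairing across epochs would rescue the test, and then the text needs to say so; either way it needs correcting.

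The effect is most direct on dPLI and unthresholded wPLI. It is less certain for graph properties and hubs. Spectral features and inter-subject correlations are unaffected.

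**What to change.** Replace the signed-rank comparison with a rank or percentile rule, and state the level and sidedness:

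- **wPLI:** keep a value only if it exceeds the 95th percentile of its own surrogates (one-sided); otherwise set it to 0.
- **dPLI:** keep a value only if it lies outside the 2.5th to 97.5th percentiles of its own surrogates; otherwise set it to 0.5.
- **Number of surrogates:** raise it above 20. Two-sided 5% needs at least 39, and 1000 would match the Auditory Narrative analysis. Raising the number without changing the test is not a remedy.
- **If pairing across 10-s epochs is what is meant:** describe the pairing, the number of epochs and the quantity paired.

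False discovery rate control across pairs is optional and needs enough surrogates to be workable. For 8,128 pairs (an upper limit) at 5%, the number of pairs that must beat every surrogate before any is kept is 8,128 × (1/301)/0.05 ≈ 540 with 300 surrogates, and 8,128 × (1/1001)/0.05 ≈ 163 with 1000.

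The costs are revised wording, more computing time and sparser matrices. Because more wPLI values become zero, check that the spanning graph that sets each patient's threshold can still be formed. The change applies to stored recordings and alters no patient procedure.

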#### Graph Theoretical Brain Network Properties

The functional brain network of each frequency band (i.e., delta, theta, alpha, beta) will be constructed using the wPLI of all pairwise combinations of electrode channels. We will then construct a binary adjacency matrix A_*ij*_ using a custom threshold for each participant: if the wPLI*_*ij*_* value of nodes *i* and *j* are above the custom threshold of all wPLI values, A*_*ij*_* = 1; otherwise, A*_*ij*_* = 0. The custom threshold will be determined by identifying the lowest threshold enabling a minimally-spanning graph during the interruption of sedation, which will be considered the more naturalistic brain network of the three recordings. This will enable a more accurate construction of each patient’s brain network, based on how their brain injury affects connectivity characteristics. From the binary adjacency matrix, we will calculate basic graph theoretical network properties, including global efficiency (Latora and Marchiori, 2001), clustering coefficient (Watts and Strogatz, 1998), modularity (Newman, 2006), and binary small-worldness (Humphries and Gurney, 2008).

Hub nodes are highly-connected nodes, considered to play a vital role in the structure of a network and the flow and integration of information within the network (van den Heuvel and Sporns, 2013). In healthy individuals, their structure and topographical location become altered under anesthesia (Lee H. et al., 2013) Using the network of each frequency band, network hubs will be calculated using node degree (i.e., the number of edges connected to a node) and betweenness-centrality (i.e., the number of shortest paths passing through a node).

